## Background

Traumatic brain injury (TBI) is caused by a violent force that affects the head directly or indirectly, and is the leading cause of death and disability among young people around the world [1]. According to epidemiological survey results and expert prediction, by 2020 TBI will become the third largest disease burden in the world. Disorders of consciousness (DOC) refers to the serious impairment of patients’ ability to recognize and perceive the surrounding environment and their own state, which can include coma, vegetative state (VS)/unresponsive wakefulness syndrome (UWS) and a minimally conscious state (MCS) [2]. Many patients with severe TBI will suffer from DOC, and up to 14% of patients with TBI are in a long-term coma or persistent VS after rescue; the longer the duration of coma, the higher the mortality [3, 4]. Therefore, early awakening of patients with TBI can reduce the disability rate and mortality in patients with TBI.

There has been extensive clinical and basic research into treatments for DOC treatments, including electrical nerve stimulation: in DOC this mainly involves median nerve electrical stimulation (MNES) [5–7], spinal cord electrical stimulation (SCS) [8–10], transcranial direct current stimulation (tDCS) [11–13], vagus nerve stimulation (VNS) [14, 15], or deep brain stimulation (DBS) [16, 17]. However, there is no unified DOC treatment guideline [18].

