### Inclusion and exclusion criteria for the trial

Patients who meet the following criteria will be deemed eligible for the trial: coma: (1) male or female patients aged 18–65 years; (2) severe traumatic brain injury that leads to coma; (3) coma that lasts more than a week; (4) magnetic resonance imaging (MRI) of the head demonstrates no obvious shift, structural damage, extensive necrosis of the brain structure change and obvious brain stem (not including the pyramidal tract) or thalamic lesions with lesions in each lobe not exceeding 30% of the scope of one side of the brain; (5) stable condition and stable vital signs; and (6) the families of the patients volunteered the patient to participate in the study and provided signed informed consent.

VS/UWS and MCS: (1) male or female patients aged 18–65 years; (2) diagnosis as established by the Multi-Society Task Force in 1994 and the current internationally recognized standards for plant status diagnosis; conforming to the current internationally recognized minimum state diagnostic criteria for international studies, such as reported by Giacino in 2002; (3) the course of illness is more than one month; (4) MRI of the head demonstrates no obvious shift, missing, extensive necrosis of the brain structure change and obvious brain stem (not including pyramidal tract) or thalamic lesions, with lesions in each lobe lesions not exceeding 30% of the scope of one side of the brain; (5) stable condition and stable symptoms; (6) the families of the patients volunteered the patient to participate in the study and provided signed informed consent .

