Patients who meet the following criteria will be excluded from the trial: (1) the use of sedative sleeping pills, anesthetics, psychotropic drugs, muscle relaxants or Na^+^ and Ca2^+^ channel blockers (such as carbamazepine, etc.) during the evaluation period; (2) ventilator dependence; (3) the course of illness is longer than 1 year; (4) The presence of any materials within the body that would contraindicate MRI, such as pacemakers, dentures, metal prostheses, etc., or open craniocerebral injury or skull defects that would contraindicate electromagnetic stimulation; (5) history of epileptic seizures or epileptic seizures confirmed clinically by EEG; (6) comorbid serious diseases (such as heart, liver, and kidney failure); (7) progressive neurological diseases such as central nervous system tumor or transsexual disease; (8) fever, electrolyte disturbance or unstable vital signs; (9) pregnancy; (10) local skin injury or inflammation; (11) hemostasis, coagulation, and anticoagulation dysfunction, as well as people on anticoagulants; (12) acute massive cerebral infarction; and (13) hyperalgesia in the stimulus area.

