### Data collection and management

General baseline information will be collected about patients when they are sent to the hospital and will include the following: age, sex, nationality, education level, disease type, course of illness. Major indicators are assessed at the end of the 1st, 2nd, 3^rd^, and 4th week of treatment, including application of the GOS after 4 weeks of treatment, all secondary index evaluations: the BAEP, body feeling on USEP, and EEG data. For each treatment, safety is assessed in terms of adverse events and adverse reactions.

Outcomes will be assessed using the GOS at the end of 1st, 2nd, 3rd, and 4th week, and will be performed using the BAEP, USEP, and EEG at the end of the 4th week of treatment. Complications during follow up will also be assessed. If the patient is still in the hospital, the investigator may visit the patient on the ward to go through the evaluation. If the patient has been discharged, his or her legal representative will be told to come back in due time for assessment after leaving the hospital. If the patient does not arrive, the investigator will try to contact the patient or the family members by telephone. Other possible methods may also be used to explain the situation and complete the outcome assessment. If all attempts fail, no further contact will be made, and the patient will be recorded as lost to follow up.

All the data will be collected by independent investigators who are blind to the patient’s allocation. Each local study center will assign a specific investigator at the beginning of the trial. This investigator will be excluded throughout treatment of all the participants unless asked by clinicians to perform the assessment.

All variables specified in the protocol will be documented on standardized hard-copy case report forms (CRFs) in all participating centers. When the 8-week follow up is complete, data in the CRF of each patient will be validated for completeness, consistency, and plausibility, by an independent investigating physician in a local center. Then the CRF will be transmitted to the Center of Evidence Based Medicine, NCU, which will be responsible for the development of a central database, and data entry and storage. At the end of the trial, the database will be locked and sent to the study statistician for analysis based on a predetermined statistical analysis plan.

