### Statistics methods

#### Statistical analysis

SPSS21.0 software will be used to analyze the test results. In the descriptive analysis of the sample, continuous variables will be expressed by mean and standard deviation for normally distributed data, and median and interquartile range for non-normally distributed data. Normally distributed data variables will be statistically compared between groups using the *t* test. Ordinal-level variables with a non-normal distribution will be statistically compared between groups using the Mann–Whitney *U* test. Measures with a discrete distribution will be expressed as percentages and analyzed using the chi-squared (χ2) or Fisher’s exact test as appropriate. A general linear model or logistic regression model will be applied to adjust for confounding influences if necessary.

We will compare baseline characteristics between groups using the *t* test or Mann–Whitney test for continuous variables and the Pearson chi-squared or Fisher’s exact test for categorical variables. If statistical significance appears, the inequality factors will be treated as confounding variables in the final efficacy analysis. For comparison of the primary or secondary outcomes between groups, the *t* test or non-parametric tests will be used to analyze continuous data, and the Pearson chi-squared or Fisher exact test to analyze categorical data. To control for possible confounding variables, linear models or linear regression will be applied for dependent continuous variables and logistic regression models for dependent categorical variables. Subgroup analysis of the primary outcomes will be stratified by participants’ sex. Analysis of variance will be used for the repeated measurement data. Analysis of the primary and secondary outcomes will be on an intention-to-treat (ITT) and a per-protocol (PP) basis. The result of the ITT analysis will be compared with that of the PP analysis to determine whether the results are consistent. Missing data will be handled according to the method of last observation carried forward. Adverse events will be listed and analyzed using the chi-square test or Fisher’s exact test.

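### Baseline factors such as time since injury enter the efficacy analysis only on a significant baseline test, a chance-driven trigger that costs precision without biasing the trial overall

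*Protocol article*

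**What the plan says.** Under Statistical analysis, the protocol article compares baseline characteristics between arms with *t*, Mann–Whitney, chi-squared or Fisher tests and continues: "If statistical significance appears, the inequality factors will be treated as confounding variables in the final efficacy analysis". Primary and secondary outcomes are otherwise compared with unadjusted tests. Two further sentences allow general linear, linear or logistic models to deal with confounding where needed, but neither names a covariate.

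Under Inclusion and exclusion criteria, coma patients qualify with "coma that lasts more than a week" and vegetative or minimally conscious patients when "the course of illness is more than one month". The upper limit for everyone is an exclusion if "the course of illness is longer than 1 year".

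The Background treats duration as prognostic: "the longer the duration of coma, the higher the mortality". Data collection and management lists the baseline items as "age, sex, nationality, education level, disease type, course of illness". Under Randomization and allocation concealment, patients are grouped as coma, MCS or VS and then allocated 1:1 in blocks. Time since injury plays no part in allocation.

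**The concern.** A baseline significance test asks whether a difference between arms could be due to chance. In a properly randomised trial it is due to chance, so the test says nothing about whether a factor should be in the model. What matters is how strongly the factor predicts outcome and how far it happens to be out of balance. A rule based on the p-value ignores the first and, in a trial of 80, misses most moderate cases of the second.

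Time since injury is the clearest example. The window is about 7 to 365 days for coma (365/7, about 52-fold) and 1 to 12 months for VS and MCS (12-fold). Grouping by diagnosis therefore leaves a wide spread within each group. Three things are at stake: a final model that cannot be known until the data are seen, an estimate shifted by an uncorrected imbalance in some realised allocations, and precision given up in most trials.

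**Working it through.** **The plan's own figure.** Inputs from Sample size: difference 12.44 − 10.43 = 2.01 GCS points, SDs 2.51 and 1.90, α = 0.05, power 90%. With the larger SD and a two-sided test, n = 2(1.96 + 1.2816)² × 2.51² / 2.01² = 32.8, so 33 per group. This reproduces the stated figure. The planned effect is 2.01/2.51 = 0.80 SD. The check uses 40 per arm (randomised) and 33 per arm (evaluable).

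**What the baseline test lets through.** The SE of a standardised baseline difference is √(2/n), and the largest unflagged difference is t(0.975, 2n − 2) × SE.

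| | 40 per arm | 33 per arm |
|---|---|---|
| SE | 0.224 | 0.246 |
| Largest unflagged imbalance | 0.445 SD | 0.492 SD |
| P(imbalance > 0.3 SD) | 18.0% | 22.3% |
| less those flagged (about 5%) | 13% | 17% |

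A 0.30 SD imbalance with 40 per arm gives z = 0.30/0.224 = 1.34, p about 0.18. Of allocations with an imbalance above 0.3 SD, 13/18 (about 72%) would go uncorrected.

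**Size of the shift in one allocation.** Shift = r × imbalance, where r is the correlation of time since injury with outcome. The documents do not give r. For r = 0.3 to 0.5:
- Just below the threshold: 0.445 × r = 0.13 to 0.22 SD, or 17% to 28% of 0.80 SD. This is close to the worst unflagged case.
- At the median absolute imbalance (0.6745 × 0.224 = 0.15 SD): 0.045 to 0.075 SD, or 6% to 9% of 0.80 SD.

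**Operating characteristics.** Simulation with 20,000 trials per setting, 33 per arm, and a standard normal covariate and outcome. It compares the stated rule with adjustment fixed in advance.

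| r | Type I error: rule / prespecified | Power at 0.80 SD: rule / prespecified |
|---|---|---|
| 0.3 | 4.8% / 4.8% | 89.3% / 91.2% |
| 0.5 | 4.4% / 5.0% | 90.6% / 95.8% |
| 0.7 | 3.8% / 4.9% | 91.2% / 99.4% |

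The trigger fired in about 5% of trials at every r, including r = 0.

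**Within the 17% of trials with an unflagged imbalance above 0.3 SD** (r = 0.3 / 0.5 / 0.7):
- False-positive rate: 6.5% / 8.4% / 11.7% unadjusted, against 4.8% / 4.8% / 5.7% adjusted.
- Power: 87% / 85% / 80% unadjusted, against about 90% / 95% / 99% adjusted.

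**The case against.** A reader might infer that spontaneous recovery can pass for a tDCS effect across the trial as a whole. The documents do not support that. Allocation is 1:1 with a concurrent sham arm, so natural recovery occurs in both arms, and overall type I error under the rule is at or below 5%. The false-positive excess exists only conditionally, in allocations where an imbalance arose and was missed. For the same reason, the absence of a run-in is not an error.

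The size can also be overstated. The 17% to 28% figure is a near-threshold case, is benchmarked on GCS (a secondary outcome), and should not be read as the expected bias. Grouping by diagnosis before allocation should shrink imbalances somewhat if time since injury differs by type, as the different entry limits suggest; the calculation ignores this. The correlation is assumed: the Background links coma duration to mortality, not time since injury at entry to 4-week GOS or GCS. At r = 0.3 the power loss is about 2 points. All of this stands, and it limits the point to precision and conditional bias.

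It can also be said that the article's other adjustment sentences leave room for covariates, and that the predetermined analysis plan it mentions, which is not shown, may list them. That is fair as far as a missing covariate list goes, which is no fault here. It does not rescue the stated trigger: an analysis plan consistent with the article would inherit it.

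**Conclusion.** The point holds in a limited form. The article states a rule that chooses covariates by chance and makes the final model data-dependent. With 40 per arm it leaves imbalances of up to about 0.445 SD uncorrected (0.49 SD with 33), and an unflagged imbalance above 0.3 SD occurs in about 13% of trials (17% with 33). There is no systematic bias and no inflation of overall type I error.

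The average cost is about 2 points of power at r = 0.3 and 5 at r = 0.5, plus a conditional bias in unlucky allocations. These sizes rest on the assumed correlation, a continuous and roughly normal outcome, and simple randomisation without the diagnostic grouping. They are indicative for GCS and only a rough guide for the five-level GOS. The trial is not invalidated, but the rule should be changed before unblinding.

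**What to change.** Delete the significance trigger. State instead that, whatever the baseline p-values, the efficacy analyses always adjust for:
- type of consciousness disorder (coma, MCS, VS), since patients are grouped by it before randomisation;
- time since injury at randomisation, on the log scale;
- for GCS, the baseline GCS.

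Name the models: linear for GCS, ordinal logistic for GOS. Baseline characteristics can still be tabulated descriptively by arm.

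The cost is a few degrees of freedom and slightly more analysis work, because the default tests give way to models. Course of illness and baseline GCS are already recorded. One thing to confirm is that the case report form allows days from injury to randomisation to be derived, since the article describes course of illness as collected when patients come to hospital. The adjusted odds ratio for GOS is conditional on the covariates and should be reported as such.

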### Outcome measures

In this study, primary outcomes will be measured at baseline and the end of every week from the 1st to the 4th week. Secondary outcomes will be measured at baseline and the end of the 4th week. During each treatment, adverse events and untoward effects will be assessed. After follow up (8 weeks), the prognosis and disability condition outcomes (GOS and Disability Rating Scale (DRS)) will also be evaluated. All outcome assessments will be independently performed by experienced and blinded assessors, the same one professional rehabilitation physician. A summary of all the measures in the trial is shown in Table 1.

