### Primary outcomes

#### Glasgow Outcome Scale

The GOS is used to assess the recovery and outcome of patients with TBI. The severity of disability is divided into 5 levels according to indicators such as whether the patients can recover to undertake work, study, and self-care. The 5 levels are death, vegetative state, severe disability, moderate disability and good recovery.

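### The protocol names no deciding visit and no deciding test for its only primary outcome, the five-level GOS measured at weeks 1 to 4

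*Protocol article*

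**What the plan says.** **Timing.** The Outcome measures section states that "primary outcomes will be measured at baseline and the end of every week from the 1st to the 4th week". The abstract, Study design and Data collection and management give the same weekly schedule. The nearest thing to a single time point is the phrase "including application of the GOS after 4 weeks of treatment" under Data collection and management. It stands in a sentence that lists all four weeks, and the next paragraph lists all four again. A later reading is described separately: "After follow up (8 weeks), the prognosis and disability condition outcomes (GOS and Disability Rating Scale (DRS)) will also be evaluated".

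**Scale.** "The 5 levels are death, vegetative state, severe disability, moderate disability and good recovery" (Glasgow Outcome Scale section).

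**Tests.** The Statistical analysis section assigns no test to GOS by name. It gives general rules:
- "Ordinal-level variables with a non-normal distribution will be statistically compared between groups", with the Mann-Whitney test named as the method.
- "Measures with a discrete distribution will be expressed as percentages and analyzed using the chi-squared" or Fisher's test.
- For primary and secondary outcomes, the t test or "non-parametric tests will be used to analyze continuous data, and the Pearson chi-squared or Fisher exact test to analyze categorical data".
- "Analysis of variance will be used for the repeated measurement data".

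The protocol sets a 5% type I error in its sample size section and does not say how that error is spread over visits. It refers to a predetermined analysis plan, which is not available here.

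**The concern.** A confirmatory trial needs one comparison, fixed in advance, that decides whether the treatment worked. Here two choices are open.

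- **Which visit.** Four weekly readings share primary status, and no rule says which one, or which summary of them, decides.
- **Which test.** A repeated five-level score is at once ordinal, discrete and a repeated measurement, so several of the general rules apply to it. They also ask different questions. ANOVA compares means of level codes and treats the steps from death to good recovery as equally spaced. A rank test uses the order only. Unordered chi-squared ignores the order.

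Two things are at stake. The nominal 5% error rate is not protected if visit or test is settled after the data are seen. And if the chi-squared rule were the one applied, a trial of 80 patients would lose much of its ability to detect an ordered shift.

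**Working it through.** **1. The plan's own figure.** The Sample size section gives 33 per group. With its formula, two-sided 5% alpha, 90% power, SD 2.51 and a difference of 2.01:

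n = 2 × (1.960 + 1.282)² × 2.51² / 2.01² = 32.77, rounded up to 33.

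The figure reproduces, but it is for the Glasgow Coma Scale, a secondary outcome. It shows no power for GOS and does not bear on the choice of visit or test. From that section I take only alpha = 0.05 and 40 per arm.

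**2. Error rate if any one of four weekly tests counts.** The protocol does not state this procedure; the calculation shows what the open wording would allow.

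- Independent tests (upper end): 1 − 0.95⁴ = 0.185.
- Correlated tests: P(largest |Z| of four > 1.96), simulated with normal statistics under equal correlation and under first-order autoregressive correlation. The protocol gives no correlation, so a range is shown.

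| Assumed correlation | Equal | Autoregressive |
|---|---|---|
| 0.95 | 8.0% | 8.7% |
| 0.9 | 9.4% | 10.4% |
| 0.7 | 13.1% | 14.3% |
| 0.5 | 15.6% | 16.6% |

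If the test could also be picked (t, Mann-Whitney or five-level chi-squared at any of the four weeks), a simulation under no effect gave about 24% and 22% at latent autoregressive correlations of 0.7 and 0.9. It used 40 per arm and an assumed GOS distribution of 5/45/40/8/2%.

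**3. Power of the permitted between-group tests at one visit.** The protocol gives no GOS distribution or expected effect, so these are assumptions. Take the control arm as 10/30/40/15/5% from death to good recovery, 40 per arm. For a common odds ratio OR, the active-arm odds of being at or below a level equal the control odds divided by OR. For OR = 3:

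- Control cumulative: 0.10, 0.40, 0.80, 0.95. Odds: 0.111, 0.667, 4, 19.
- Divided by 3: 0.037, 0.222, 1.333, 6.333. Cumulative: 0.036, 0.182, 0.571, 0.864.
- Active arm: 3.6/14.6/39.0/29.2/13.6%.

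Simulated power at two-sided 5%:

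| OR | Unordered chi-squared | Mann-Whitney |
|---|---|---|
| 2 | about 21% | about 38% |
| 3 | about 52% | about 75% |
| 4 | about 75% | about 91% |

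Two other assumed control distributions (5/45/40/8/2% and 5/30/40/20/5%) at OR 2.5 gave 32% and 36% for chi-squared, 58% and 60% for Mann-Whitney, and 55% and 60% for the t test. So the loss belongs to chi-squared. The rank test has none, and the t test costs little power; the objection to it is equal spacing.

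**The case against.** Several points on the other side are sound and limit the finding.

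- **A reader might infer that ordinal information is lost.** The text does not support that. The Mann-Whitney rule for non-normal ordinal variables is arguably the rule that fits GOS most closely, and it keeps the order. The loss is conditional on GOS being handled as discrete or categorical data. What stands is that the later sentence on comparing outcomes mentions only continuous and categorical data, so the text does not settle which rule governs.
- **A reader might infer that four tests at 5% are planned.** Nowhere is it said that each week is tested at 5%, or that one significant week means success. A single repeated-measures ANOVA over all visits would be one overall test, not four chances. What stands is that ANOVA is not called the primary analysis, and the deciding effect (group or group by time) is not given.
- **A reader might count the 8-week GOS as a fifth primary reading.** Outcome measures confines the primary outcomes to baseline and weeks 1 to 4 and lists the follow-up GOS apart, with the disability scale.
- **The correlations may be high.** A coarse scale read weekly, with last observation carried forward, may change little between visits. That argues for the lower end of the range, still above 5%.
- **The unseen analysis plan may settle this.** It may. But the deciding time point and test of the primary outcome are core protocol content, and the published rules overlap on that very outcome.
- **The analyst is blinded to group labels.** Under Blinding, the analyst sees two unlabelled groups. That hides the direction of a result, but a visit or test can still be chosen by its two-sided p-value.

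**Conclusion.** The concern holds in this form: the protocol fixes neither the visit or summary nor the test that decides its only primary outcome, and it has no multiplicity rule. The primary result can therefore be chosen after the data are seen. This follows from the text and needs no assumption.

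The sizes are conditional illustrations. If any of four weekly 5% tests counted as success, family-wise error would be about 8% to 17% at assumed correlations of 0.95 to 0.5. If the unordered chi-squared route were taken, power would be about 52% against 75% at an assumed OR of 3. If the primary analysis is in fact one prespecified Mann-Whitney test at one visit, neither cost arises; the protocol only has to say so. Because the confirmatory claim depends on it, this must be fixed before any unblinded look at outcome data.

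**What to change.** - **One time point.** Name a single primary comparison, for example GOS at the end of week 4 in all randomised patients.
- **One order-preserving analysis.** Preferably a proportional-odds model with treatment, type of consciousness disorder (coma, vegetative state or minimally conscious state, the grouping used at randomisation) and a baseline severity score already collected, such as the Glasgow Coma Scale, reported as a common odds ratio with confidence interval. A prespecified Mann-Whitney test stratified by type of disorder would also cure the fault.
- **Other readings secondary.** Label GOS at weeks 1 to 3 and at 8 weeks after treatment as secondary. If all four weeks must stay primary, state a multiplicity rule; Bonferroni would give 0.05 / 4 = 0.0125 each.
- **Remove the alternatives for GOS.** Drop unordered chi-squared, ANOVA on level codes and any choice of test by observed normality.

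The cost is wording in the protocol and analysis plan, with no new data or patients. The downsides are that the common odds ratio rests on proportional odds, which should be examined, and that the other weeks lose confirmatory status.

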### Sample size

The sample size calculation is based on improvement in scores on the Glasgow coma scale (GCS). According to similar published articles [25], the GCS scores after active tDCS and sham tDCS are respectively (12.44 ± 2.51) and (10.43 ± 1.90), *n* = 38. According to a similar study [26], treatment with conventional rehabilitation combined with tDCS can probably improve the GCS by 2.01 points on average in participants receiving this intervention compared to those in the control group. Improvement will be measured according to the same sample size of the estimation formula:
$$ n=2\left[{\left({u}_a+{u}_{\beta}\right)}^2{\sigma}^2\right]/{\delta}^2 $$

With a type I error of 5% (*α* = 0.05) and 90% power (*β* = 0.10), the estimated required sample size is 33 participants per group. Allowing for a 20% dropout rate during the study, a minimum total of 80 participants is needed to reach the target of 40 participants per group.

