### Study endpoints

The study endpoints are as follows:
If serious adverse reactions occur during the test, the test will be terminated in time to protect the subjectsIn the case of serious complications or deterioration of the condition of the subject in the test, the test will be terminated if emergency measures are requiredIf the subject is required to withdraw from the clinical study, the test will be terminatedIf the patient is not cooperative and does not obey the treatment, and the treatment staff repeatedly explains that the treatment is ineffective, the test will be suspended

The investigator will record in detail the reason and time of a participants’s withdrawal from the study.

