### Safety assessments

The medical staff will record adverse events (AEs) that occur at any time during treatment. When a serious AE occurs, the Ethics Committee of the First Affiliated Hospital of Nanchang University will determine whether the participant needs to be withdrawn from the study. We will treat AEs free of charge.

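### Last observation carried forward is the only missing-data rule for a primary outcome whose lowest level is death, and the protocol does not say how deaths or patients withdrawn on deterioration are scored

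*Protocol article*

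**What the plan says.** All references are to the protocol article.

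- **Missing data (Statistical analysis).** "Missing data will be handled according to the method of last observation carried forward". No exception is made for death or deterioration. Primary and secondary outcomes are analysed by intention to treat and per protocol, and the two results are compared.
- **Primary outcome (Glasgow Outcome Scale; Outcome measures).** "The 5 levels are death, vegetative state, severe disability, moderate disability and good recovery". On timing, "primary outcomes will be measured at baseline and the end of every week from the 1st to the 4th week". A further GOS, with the Disability Rating Scale, is planned later: "After follow up (8 weeks), the prognosis and disability condition outcomes".
- **Leaving the study (Study endpoints).** The test ends for a subject with a serious adverse reaction. It also ends in "the case of serious complications or deterioration of the condition of the subject in the test", with the qualifier that emergency measures are required. What is then recorded is the reason and time of withdrawal: "The investigator will record in detail the reason and time of a".
- **Serious adverse events (Safety assessments).** The ethics committee "will determine whether the participant needs to be withdrawn from the study".
- **Contact (Follow up; Data collection and management).** Telephone contact every two weeks during follow-up records medications and rehabilitation therapies. For outcome assessment, ward visits, recall after discharge, telephone calls and other means are planned before a patient is recorded as lost.
- **Expected loss (Sample size).** "Allowing for a 20% dropout rate during the study", giving 40 per group.

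**The concern.** Some of the protocol's exit routes are themselves bad clinical events, so a missing GOS after such an exit is linked to the value that would have been seen. Last observation carried forward fills the gap with a score taken before the event. It also works the other way: a patient lost while improving keeps an early, low score. In both cases the filled value is analysed as if observed.

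The primary intention-to-treat comparison is at stake, and with it part of the safety objective, because death is a level of the primary scale. If exits or their reasons differ between arms, the estimated effect can move in either direction. The comparison with the per-protocol result does not test the carry-forward assumption.

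**Working it through.** **1. The plan's own figures.** The protocol gives no rate of death, deterioration or exit by reason. The only related figure is the dropout allowance. The formula under Sample size, with a standard deviation of 2.51, a difference of 2.01, two-sided 5% and 90% power, gives 2 × (1.960 + 1.282)² × 2.51² / 2.01² ≈ 32.8, so 33 per group, as stated. Then 33 × 1.2 = 39.6, rounded to 40. Twenty percent of 40 is 8 patients per arm, from all causes.

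**2. What carry-forward can assign.** Number the levels 1 (death) to 5 (good recovery); the numbering is an assumption, the order is the protocol's. A GOS recorded in a living patient is at least 2, so a carried-forward score can never be 1. A death left as missing is scored at least one level too high. A patient last scored 2 who would have reached 3 is scored one level too low. Each one-level error moves the mean of a 40-patient arm by 1/40 = 0.025.

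**3. Shift in the difference.** If *k* deaths in an arm of 40 are carried forward at level *L*, the arm mean is overstated by *k*(*L* − 1)/40. The bias in active minus sham is the difference between the two overstatements. The counts below are assumed.

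| Deaths left missing, active / sham | *L* = 2 | *L* = 3 |
|---|---|---|
| 4 / 4 | 0 | 0 |
| 8 / 8 | 0 | 0 |
| 6 / 2 | +0.10 | +0.20 |
| 8 / 4 | +0.10 | +0.20 |
| 4 / 8 | -0.10 | -0.20 |

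**4. One worked illustration.** Assume 15% of active and 5% of sham patients (6 and 2 of 40) exit on deterioration and die, with none of these deaths entered as a GOS score. Assume survivors in both arms are spread 40/45/12/3% over GOS 2 to 5. Their mean is 2(0.40) + 3(0.45) + 4(0.12) + 5(0.03) = 2.78.

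- Deaths scored 1: active 0.85 × 2.78 + 0.15 × 1 = 2.513; sham 0.95 × 2.78 + 0.05 × 1 = 2.691; difference -0.178.
- Carried forward at 2: active 2.363 + 0.30 = 2.663; sham 2.641 + 0.10 = 2.741; difference -0.078.
- Carried forward at 3: active 2.363 + 0.45 = 2.813; sham 2.641 + 0.15 = 2.791; difference +0.022.

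At level 2, 0.100 of 0.178, or 56%, of the assumed harm disappears.

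**5. Set against sampling error.** With deaths scored 1, the variances are 0.85 × 8.32 + 0.15 − 2.513² = 0.907 (active) and 0.95 × 8.32 + 0.05 − 2.691² = 0.712 (sham), where 8.32 is the survivors' mean square. The standard error of the difference is √[(0.907 + 0.712)/40] ≈ 0.20. The assumed true difference is less than one standard error.

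**The case against.** A reader might infer that the plan necessarily scores the sickest patients at their pre-deterioration level and hides deaths. The documents do not support that.

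- Carry-forward applies only to missing values. Death is a listed GOS level, so a known death can be entered as a score, and nowhere is a known death said to be treated as missing.
- The deterioration rule applies only if emergency measures are required, and withdrawal after a serious adverse event is decided case by case.
- Active attempts to complete the outcome assessment are planned, as is an 8-week GOS. Withdrawn patients are not excluded from either.
- A patient last scored as vegetative who worsens but survives stays at that level, so carry-forward gives the right score.
- Harm is also tracked outside the GOS: adverse events are recorded and compared between arms, complications are recorded at each visit, and a monitoring committee is in place.
- The illustration rests wholly on assumed rates. With equal losses and equal last values the bias in the mean difference is zero.

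All of this stands, and it limits the point to a possible bias. It does not remove it. The contact provisions do not expressly cover patients withdrawn under Study endpoints, for whom only reason and time must be recorded, and the telephone calls are not described as collecting vital status. Whether a death becomes a GOS score is left to the assessor. Table 1 also shows no GOS at screening although the text promises one at baseline, so a week-1 exit might have nothing to carry forward.

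An analysis plan is mentioned but not shown, and sensitivity analyses could properly sit there. The primary method, however, is already fixed in the protocol.

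**Conclusion.** The point holds as a weakness in a stated choice. Last observation carried forward is the sole missing-data rule for a scale that includes death, patients can leave the study because of bad events, and neither continued GOS assessment nor the scoring of death is settled for them. The intention-to-treat comparison may be biased if losses or their reasons differ between arms.

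The documents fix neither direction nor size. The change from -0.18 to -0.08 is illustration only: it assumes 15% versus 5% exits ending in death, none entered as a score, all carried forward at GOS 2, and identical survivors. Reversing the imbalance reverses the bias, and equal losses with equal last values leave the mean difference unbiased. It would be wrong to conclude that the result will be biased, or that it will favour active stimulation.

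**What to change.** Leave the stopping rules unchanged, and:

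1. State that stopping stimulation does not stop assessment. Weekly GOS to week 4, the 8-week GOS and vital status are collected for every randomised patient, using the contacts already planned under Follow up and Data collection and management.
2. Score every known death at the lowest GOS level at that visit and all later ones.
3. Replace last observation carried forward as the primary method with multiple imputation or a likelihood-based ordinal model, using arm, type of disorder of consciousness, baseline GOS and prior GOS.
4. Because these methods usually assume data missing at random, add a delta-adjusted or worst-case sensitivity analysis. Keep carry-forward at most as a further sensitivity analysis.

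The cost is a few sentences of protocol text, slightly more analysis work and some follow-up effort for withdrawn patients. Items 1 and 2 matter most and need to be in place before enrolment, because outcomes that were never collected may not be recoverable.
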